### Inclusion criteria

All children will participate in Tier 1. Children in grades 4–8, who meet screening and diagnostic criteria will be included in Tier 2. The screening criterion is a score ≥1 SD on the Conduct Problems or Emotional Symptoms scales of the Strengths and Difficulties Questionnaire (SDQ), a widely-used screening instrument [78], filled out by a teacher. Children meeting screening criterion will undergo a diagnostic evaluation. Children meeting primary diagnosis of ODD, CD, GAD, SAD, or SP (based on a parent structured interview [79] and a symptom severity scale [80] filled out by an independent rater) at Intermediate or Positive level will be eligible for participation. Children with comorbid (secondary) conditions will be included.

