### Child outcome measures for at risk/high risk children

Children’s diagnostic status, mental health symptoms, coping skills and functional impairment will be assessed at pre- and post-participation in CPP and FRIENDS. All of the parent measures are available in Spanish. Diagnostic status will be assessed via a computerized parent-structured interview [79,104]. This instrument reports three levels of diagnostic severity for each disorder: Positive, Intermediate (at-risk), or Negative. Upon completion of the structured interview, the independent evaluator (IE) will assign interference scores to each positive diagnosis in order to determine primary and secondary diagnoses [80], based on a seven-point scale, with lower scores indicating less severity. Changes in coping skills will be assessed via a 34-item self-report questionnaire [105] that measures coping strategies (seeking social support, self-reliance/problem-solving, distancing, internalizing, and externalizing). The total score for this measure will be used in outcome analyses.

Changes in mental health symptoms (*e.g.*, aggression, conduct problems, anxiety, somatic symptoms) will be measured via parent [106], child [107,108] and teacher [106] multi-axial rating scales. Teachers will also provide changes in children’s grades and rate of academic productivity [109]. After all parent, child and teacher data are collected at pre- and post-, the IEs will complete a measure of functional impairment [110].

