Changes from pre- to post- implementation in diagnostic status, symptom severity and impairment level, coping skills and academic productivity during Implementation across all schools, regardless of level of support, will be analyzed using McNemar tests. For each of the listed primary outcomes, a series of 2X2 tables will be constructed to test changes from pre- to post- in the pertinent categories using McNemar tests. Alpha level will be adjusted to 0.025 based on Bonferroni criteria for multiple comparisons. We will also use McNemar tests to test the hypothesis that the pre- to post- level of improvement in diagnostic status, symptom severity, impairment level, coping, and academic productivity obtained during Implementation will be maintained during Sustainability among schools receiving C + C.

We would like to determine whether pre- to post- improvement in diagnostic status, symptom severity, impairment level, and academic productivity differ by support condition during the implementation phase. In addressing this research question, and for the sake of simplifying the statistical analysis, each student will be categorized as either improved or not improved based on change from pre- to post-. A category one will be assigned if a student’s diagnostic status, for example, changes either from positive to intermediate, intermediate to negative, or positive to negative. Otherwise a score of zero will be assigned. Similar coding will be used for symptom severity, coping, impairment level, and academic productivity. We will use chi-squared tests to compare the proportion of (yes/no) for each of the primary outcomes between C and C + C type of supports. To examine changes in the rate of ODRs between baseline and follow up during each school year, the number of students with at least one ODR will be defined at baseline and at the follow up and a 95% confidence interval for such changes will be constructed for each of the five years.

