### Sample size justification and statistical power

Sample size estimation was based on addressing the primary outcome, the participants’ diagnostic status (aim two). The statistical analysis will be McNemar tests for two correlated proportions (pre/post) between two groups. With a sample size of 300 students, the statistical test achieves 92% power to detect an odds ratio of three using a two-sided McNemar test with a significance level (α ) of 0.01. The odds ratio is equivalent to a difference between two paired proportions of 0.25, which occurs, for example, when the proportion among students diagnosed with a Positive anxiety/externalizing disorder at pre and improved to Intermediate at post (cell 1,2 in the 2X2 McNemar table) is 0.425 and the proportion among students diagnosed without Positive anxiety/externalizing disorder who became either Intermediate or Positive at post (cell 2,1 in the 2X2 McNemar table) is 0.175. Therefore, the proportion of discordant pairs is 0.60. We adjusted α level to 0.01 to account for the multiple 2X2 McNemar testing. We need to recruit six schools, grades four to eight,to be able to enroll 300 evaluable students who meet inclusion criteria. We assumed that the observed changes in students’ diagnostic status within schools are independent based on an evaluation of the FRIENDS program, in which ‘schools’ level accounted for less than 5% of the total variance across dependent measures.

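### Yes/no coding of Tier 2 outcomes gives away information in the comparison of support levels, and the sample-size cells contradict the plan's own definition of improvement

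*Protocol article*

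**What the plan says.** Two analyses are involved, and they should be kept apart.

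**Comparison of C with C + C** (Protocol article, Data analytic plan). The article says that "for the sake of simplifying the statistical analysis, each student will be categorized as either improved or not improved based on change". For diagnosis, a child scores 1 if the status "changes either from positive to intermediate, intermediate to negative, or positive to negative"; "Otherwise a score of zero will be assigned". The rule is then extended: "Similar coding will be used for symptom severity, coping, impairment level, and academic productivity". The test is stated too: "We will use chi-squared tests to compare the proportion of (yes/no) for each of the primary outcomes between C and C + C". No cut-point for any score is given.

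The underlying scales are finer. Under Child outcome measures, "This instrument reports three levels of diagnostic severity for each disorder: Positive, Intermediate (at-risk), or Negative"; interference is rated on seven points; coping is a 34-item questionnaire whose total is said to enter the outcome analyses.

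**Pre–post change** (Sample size justification and statistical power). This is a McNemar test. Cell 1,2 (0.425) holds children Positive at pre who improved to Intermediate. Cell 2,1 holds children not Positive at pre, with a "disorder who became either Intermediate or Positive at post (cell 2,1 in the 2X2 McNemar table) is 0.175". Under Inclusion criteria, children whose primary diagnosis is "at Intermediate or Positive level will be eligible for participation".

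**The concern.** For the arm comparison, the only reason given for the coding is simplicity. The code 0 mixes children who stayed the same with children who got worse, and the code 1 mixes small with large gains. The chi-squared test does not condition on where a child started, although a Positive child has two ways to improve and an Intermediate child only one. The choice also sits badly with other parts of the article: mixed models and GEE are called the general approach, the coping total is to be analysed, and Challenges and limitations promises a nested analysis for aim two. At stake is power in a comparison of about 153 children per arm.

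For the pre–post test, the two cells that size the trial do not follow the rule by which improvement is defined elsewhere, so the power statement describes a different event from the analysis.

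**Working it through.** **1. The plan's own power figure.** Inputs (sample-size section): n = 300, two-sided alpha 0.01, cells 0.425 and 0.175. Difference d = 0.25; discordant proportion s = 0.60.

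Power = Φ[(√n·d − z·√s)/√(s − d²)] = Φ[(4.330 − 2.576 × 0.7746)/√0.5375] = Φ[(4.330 − 1.995)/0.733] = Φ(3.18) = 99.9%.

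The article states 92%. With n = 150 the same formula gives Φ[(3.062 − 1.995)/0.733] = Φ(1.455) = 92.7%, so the stated power fits about half the stated sample. The cells give an odds ratio of 0.425/0.175 = 2.43, not three. None of these figures allows for clustering.

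**2. The cells against the improvement rule, primary diagnosis.** Eligible children enter at Intermediate or Positive, so a child who is not Positive at entry is Intermediate.

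| Entry → post | Data analytic plan | Sample-size cells |
|---|---|---|
| Positive → Negative | improved | in neither discordant cell |
| Positive → Intermediate | improved | 1,2 (improved) |
| Positive → Positive | 0, unchanged | concordant |
| Intermediate → Negative | improved | in neither discordant cell |
| Intermediate → Intermediate | 0, unchanged | 2,1 (worsened) |
| Intermediate → Positive | 0, worsened | 2,1 (worsened) |

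Intermediate at post therefore lies on both sides of the table, which no single two-way split allows. Cutting at Positive v not Positive hides Intermediate → Negative. Cutting at Negative v not Negative leaves the worsening cell empty, since nobody enters Negative.

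**3. Information lost for a score.** Assumptions: normal change score, independent children, share p improved, pre–post correlation r. The article gives neither p nor r.

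Share kept against the change score = φ(z_p)²/[p(1 − p)]:
- p = 0.5: 0.1592/0.25 = 0.637, loss 36%
- p = 0.3 or 0.7: 0.576, loss 42%
- p = 0.2 or 0.8: 0.490, loss 51%

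Against a baseline-adjusted analysis, multiply by (1 + r)/2. At p = 0.5:
- r = 0.3: 0.637 × 0.65 = 0.414, loss 59%
- r = 0.5: 0.637 × 0.75 = 0.478, loss 52%
- r = 0.7: 0.637 × 0.85 = 0.541, loss 46%

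The second set contains two choices: dichotomising, and not adjusting for baseline.

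**4. Effect on power** (153 per arm, two-sided 0.05, no clustering). A true standardised difference of 0.32 has 80% power on the score and 60% after a median split. The number per arm for 80% power rises from 154 to 242.

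**5. Clustering.** Assume 51 children per school and a school ICC of 0.01 to 0.05; the article cites under 5% of variance at school level in an evaluation of FRIENDS. For an even split the binary ICC is (2/π)·arcsin(ICC), that is 0.0064 to 0.0318. Design effects 1 + 50·ICC are 1.50 and 3.50 for the score, 1.32 and 2.59 for the binary outcome. Share kept against the change score: 0.637 × 1.50/1.32 = 72%, and 0.637 × 3.50/2.59 = 86%. Against baseline adjustment at r = 0.5 with the same ICC, multiply by 0.75: about 54–64%.

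**6. Diagnosis.** Within an entry level the coding is one cut of the three post levels. Its efficiency against a proportional-odds analysis is 3q(1 − q)/(1 − Σp_i³), where q is the share on one side of the cut and p_i are the shares at each post level. With equal thirds: 3 × (1/3) × (2/3)/(1 − 3/27) = 0.667/0.889 = 0.75, loss 25%. Over most other distributions tried the loss ran from roughly 5% to 65%, depending on where the cut falls.

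**The case against.** A pre-specified share improved is a legitimate, readable summary, improvement is measured against each child's own starting point, and the article elsewhere names mixed models and a nested analysis. That is fair, but the models are spelled out for school climate and discipline referrals, while the chi-squared test is what is stated for the child outcomes by arm. Four stronger readings are tempting and not supported:

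- *The coding mislabels unchanged children.* For diagnosis it does not: an unchanged child gets 0, not improved, which is correct. The fault there is pooling with worsening. The mislabelling appears only in the sample-size cells.
- *The pre–post test is therefore biased.* The cells are introduced as an example for a power calculation, and the analysis text speaks only of tables in the relevant categories. The verb used for cell 2,1 also suggests a change of state. Each disorder is graded separately and comorbidity is allowed, so a child may be Negative on a secondary disorder. What stands is an incoherent sample-size input on the primary diagnosis, not a proven bias.
- *Any favourable change on a score counts as improved.* This is an inference from the word similar. A fuller plan may set cut-points. That would not remove the loss: 64% kept is the ceiling for any cut of a normal change score with independent children.
- *About half the information is lost throughout.* That holds only for scores, against baseline adjustment, under an assumed correlation and no clustering.

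Tier 2 children are identified after randomisation by teams already receiving C or C + C, so entry severity could differ by arm. The article gives no size for this, and none is claimed here; it is only a further reason to adjust for entry level.

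**Conclusion.** The point stands in two limited parts.

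First, the yes/no coding with an unadjusted chi-squared test is a poor choice for outcomes measured on finer scales with a baseline already collected. Dichotomising a score costs at least about 36% of the change-score information if children are independent. The cost is smaller under clustering: 14–28% at an even split for an ICC of 0.05 down to 0.01. Adding the unused baseline brings the independent-children loss to 46–59% near an even split. These sizes rest on normality and on assumed correlations, shares improved and ICCs. For diagnosis, about 25% is a reference value only.

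Second, the sample-size cells contradict the improvement rule and the entry criteria on the primary diagnosis, and must be restated whatever analysis is used. The stated power and odds ratio do not follow from them either.

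**What to change.** **Arm comparison.** Analyse each post score in a linear mixed model with its own baseline value as covariate and school as the cluster. Compare diagnosis between arms with an ordinal model adjusted for entry level. Report percent improved by arm as a descriptive summary.

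**Pre–post test.** Define improved, unchanged and worsened by level, using the steps in the Data analytic plan, and test improved against worsened (McNemar or sign test). Restate both cell proportions, the odds ratio and the power on that definition. Use one alpha: it is 0.01 in the sample-size section and 0.025 in the Data analytic plan. A Stuart–Maxwell test on the three-by-three table should not be used, because no child can be Negative on the primary diagnosis at entry and that margin is zero by selection.

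**Cost.** A change of analysis wording and a recalculated power statement; no new data. The result becomes a mean difference or odds ratio rather than a percentage, and the school effect will be imprecisely estimated with six schools.

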## Methods/Design

Six K–8 schools in the School District of Philadelphia were randomly assigned to either Consultation or Consultation plus Coaching (See Figure 2). A stratified random assignment list of schools to condition was generated using a computerized random assignment program [77]. Schools were stratified to group one if their baseline School Climate (CREST) scores were below the median CREST scores or to group two if the CREST scores ≥ the median value. The units of analyses for Tier 1 are all of the students in those K-8 schools (650 per school), leadership team members (eight per school) and other school staff (30 per school). The units of analyses for Tier 2 are the children meeting criteria for inclusion in one of the GCBT groups (enroll a total of 367 students assuming a 17% dropout; approximately 51 eligible students per school), the school counselors (two per school) conducting the GCBT groups, and the groups themselves (14 per school; see Table 1).

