### Participants

Tier 1 research activities will include 48 teachers, administrators and parents in the leadership teams, 180 school staff for the assessment of school climate, and approximately 3,900 students. Participants in Tier 2 will be 12 counselors and approximately 306 evaluable children who have, or are at risk for, externalizing or anxiety disorders. School personnel will provide all services. Information pertaining to each school will be considered nested within school ‘cluster’ and will be defined as such in the statistical analyses.

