### Challenges and limitations

Implementing SWPBIS with mental health supports in under-resourced urban schools presents a number of challenges. In our pilot study where we developed and piloted the interventions, we faced repeated leadership changes at the district level, staff turnover at the school level, and limited parent participation [74]. However, we also found strong and consistent support among second-level administrators (*e.g.*, regional superintendents) at the District level and committed leadership teams that were able to recruit new members who functioned effectively. With the lessons learned from our pilot study, we are able to more effectively support the schools in successfully implementing SWPBIS while receiving either level of support. We have redoubled our efforts at helping schools to increase parental collaboration and support, which lead to more parent participation. We have also designed the implementation strategy to fully utilize existing policy and infrastructure (*e.g.*, implementation of District-wide practices to promote students’ success; utilizing school counselors and school facilities for Tier 2 interventions) to limit strain on resources so that the proposed program will be sustainable.

A limitation is that we are conducting the study in six schools within a single school district (though it is one of the largest and most diverse school districts in the country), which limits generalizability to schools in different parts of the country. Including a relatively small number of schools limits our ability to examine the clustering effect of school classes and schools. In this study, the unit of randomization is the school but the unit of analysis (aim two) is the student. A cluster randomized approach would have been an appropriate design if a much larger number of schools were included in the study. However, it is anticipated that the degree of similarity in treatment response among students within a class will be poorly correlated, and therefore the intraclass correlation coefficient within clusters will be small and its effect on the overall variance between schools would be minimal. However, an appropriate cluster analyses will be conducted using nested analysis. The NESTED Procedure of SAS [115] is an example of such analysis. We expect that our findings will inform implementation research in schools and procedures to be incorporated into larger-scale trials in urban schools in the future.

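### The C v C + C comparison of Tier 2 child outcomes is specified as a child-level chi-squared test although schools were randomised; this conflicts with nesting promised elsewhere and inflates false positives to roughly 8% to 30% at an assumed 5% level

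*Protocol article*

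**What the plan says.** All references are to the protocol article.

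- **Methods/Design (opening paragraph):** the six K–8 "schools in the School District of Philadelphia were randomly assigned to either Consultation or Consultation plus Coaching". Table 1 gives 153 Tier 2 children per arm, with "approximately 51 eligible students per school", so there are three schools per arm.
- **Data analytic plan, on whether improvement differs by support condition in the implementation phase:** "for the sake of simplifying the statistical analysis, each student will be categorized as either improved or not improved", and then "We will use chi-squared tests to compare the proportion of (yes/no) for each of the primary outcomes between C and C + C". The outcomes coded this way are diagnostic status, symptom severity, coping, impairment and academic productivity. No cluster term and no significance level are given for these tests.
- **Data analytic plan, general approach:** mixed models and GEE, with students nested within classes. The support-by-time interaction is interpreted for school climate and office discipline referrals (ODRs).
- **Participants:** "Information pertaining to each school will be considered nested within school", and the statistical analyses are to define it that way.
- **Sample size justification and statistical power:** changes within schools are taken as independent, because in an evaluation of FRIENDS the school "level accounted for less than 5% of the total variance across dependent measures".
- **Challenges and limitations:** "the unit of randomization is the school but the unit of analysis (aim two) is the student". It expects the effect of clustering to be minimal, and adds: "However, an appropriate cluster analyses will be conducted using nested analysis. The NESTED Procedure of SAS" is given as an example.

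**The concern.** Support level was assigned to schools, so children in one school share an assignment, a staff, a pair of counselors and a setting. Schools that differ for ordinary reasons will show different improvement rates even if coaching does nothing. A chi-squared test on children has no term for school and reads that variation as evidence about coaching.

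This is a test named for a particular comparison, with simplicity as the stated reason, not a detail left open. It cannot be squared with a statement that school data will be analysed as nested within school.

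The comparison bears directly on aim two for the children in Tier 2, and it is repeated over about five outcomes. It also feeds the cost analysis, which extends cost-effectiveness ratios to further outcomes where the results show significant improvement. A false positive could therefore reach the cost advice intended for school districts.

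**Working it through.** **The plan's own figure.** The protocol gives no power or error rate for the C v C + C comparison. Its 92% belongs to a pre/post McNemar test. From the stated cells (0.425 and 0.175, α = 0.01), the normal approximation gives 99.9% at n = 300 and 92.7% at n = 150. That mismatch is a separate matter and does not affect what follows.

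**Inputs from the protocol:** 6 schools, 3 per arm; m = 51 children per school; N = 306; school share of variance below 0.05; 84 therapy groups.

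**Assumptions:** school ICC of 0.01 to 0.05 for the improved/not-improved outcome; two-sided α = 0.05, with the protocol's other levels (0.025 for the McNemar tests, 0.01 in the sample size) as alternatives.

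**Formulas.** Design effect DE = 1 + (m − 1) × ICC. Actual false-positive rate of the unadjusted test = 2 × [1 − Φ(z / √DE)], where z is the nominal critical value.

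**At the bound:** DE = 1 + 50 × 0.05 = 3.5; 1.96 / √3.5 = 1.048; rate = 0.295.

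| School ICC | DE | Effective N of 306 | Rate at α = 0.05 | at 0.025 | at 0.01 |
|---|---|---|---|---|---|
| 0.01 | 1.5 | 204 | 11% | 7% | 4% |
| 0.02 | 2.0 | 153 | 17% | 11% | 7% |
| 0.05 | 3.5 | 87 | 29% | 23% | 17% |

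**Simulation check.** Beta-binomial data, 3 v 3 schools of 51, no true difference, 100,000 runs, improvement rates 0.30 to 0.70. At ICC 0.05 the chi-squared test rejected in 29.4% to 30.1% of runs at nominal 5%. A t-test on the six school proportions (4 df) rejected in 4.7% to 5.1% over all settings from ICC 0 to 0.05.

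**Fewer children per school.** The comparison is confined to the implementation phase, and the article text does not say how many of the 51 fall in it. Taking 25 or 34 as an assumed range at nominal 5%:
- ICC 0.01: DE = 1.24 or 1.33; rate 8% or 9%.
- ICC 0.05: DE = 2.20 or 2.65; rate 19% or 23%.

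**Therapy groups.** 306 / 84 = 3.64 children per group. An assumed extra group ICC of 0.10 adds 2.64 × 0.10 = 0.264 to DE. At school ICC 0.05 the rate goes from 29% to 31%; at 0.01 it goes from 11% to 14%. Groups add a few points at most, and at the bound the school level drives nearly all of the inflation.

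**Price of the school-level test.** With ICC 0.05 and a 50% improvement rate, SE = √(2 × 0.25 × 3.5 / 153) = 0.107. The difference detectable with 80% power is (2.776 + 0.941) × 0.107 = 0.40. Ignoring clustering it would be (1.960 + 0.842) × √(2 × 0.25 / 153) = 0.16.

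**Exact test.** There are 20 ways to split six schools 3 v 3, so an unrestricted exact two-sided test cannot go below 2/20 = 0.10.

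**The case against.** The strongest defence is that the protocol does not ignore clustering. Participants promises nesting within school, the general approach uses mixed models and GEE with an ICC in the covariance matrix, and Challenges and limitations concedes the unit mismatch, discloses the small number of schools and promises a nested analysis. This stands to a point: a reader might infer that no clustered analysis is planned, or that the chi-squared test is the only one, and the documents do not support that. But none of these statements is attached to the C v C + C comparison of child outcomes or withdraws the chi-squared tests. The mixed-model text nests by class, which leaves out the randomised unit, and ties its interaction test to climate and ODRs.

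A second defence is that an ICC below 5% is negligible. It is not with 51 children per school, since it is multiplied by 50; even 0.01 doubles the error rate. It is fair, though, that 0.05 is a bound, that it comes from a FRIENDS evaluation, and that carrying it to CPP and to a binary outcome is an assumption. Stratifying schools by baseline climate might also lower the between-school variance; the protocol gives no figure.

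Other stronger readings should be resisted:
- A flat 30% error rate: it needs the bound, an assumed 5% level and all 51 children per school.
- Therapy groups as a main cause: their contribution is small, and the documents give no group ICC.
- Confidence intervals that are too narrow: the plan names no interval for this comparison; its 95% interval in that section is for ODR changes.
- The cited SAS procedure as unsuitable: the protocol offers it only as an example, and the point does not depend on it.

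**Conclusion.** The concern holds as a conflict within the protocol. The named test for the C v C + C comparison of Tier 2 child outcomes disregards the randomised school, while other sections promise to respect it, and nothing says which prevails. If the Data analytic plan is followed as written, the false-positive rate at an assumed nominal 5% lies between about 8% and 30%, depending on the school ICC (0.01 to 0.05) and the number of children per school in the implementation phase (25 to 51). At the ICC bound with 51 per school, nominal levels of 0.025 and 0.01 become about 23% and 17%. In every case considered the level is exceeded, so the wording should be changed before the comparison is analysed.

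**What to change.** In the Data analytic plan, replace the chi-squared tests for C v C + C with a comparison of the six school-level proportions improved (three against three, t with 4 df). Report the C + C minus C difference with its 95% CI for each outcome, and keep the chi-squared table as descriptive only. A logistic mixed model with a random school effect is an obvious alternative, but its error rate with six schools has not been checked here, so the school-level analysis is the safer choice.

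Make Participants, both parts of the Data analytic plan, and Challenges and limitations agree that school is the cluster for this comparison, and state its significance level. Say also that with three schools per arm an unrestricted exact re-randomisation test cannot go below p = 0.10, so the result is an estimate rather than a confirmatory test.

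The change needs no new data. Its cost is precision: at ICC 0.05 the detectable difference is about 40 percentage points instead of the 16 that ignoring clustering would suggest, and the wider intervals reflect what six schools can show.
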